## Abstract

**Introduction:**

Surgical removal of an impacted third molar is one of the most common oral surgical procedures performed in dental offices. The postoperative phase is often associated with severe inflammation. Non-steroidal anti-inflammatory drugs (NSAIDs) are usually prescribed to manage postoperative discomfort. NSAIDs have been associated with gastrointestinal bleeding, renal function disturbances, and platelet count reductions. Thus, the present study demonstrates the utility of aescin in managing postoperative discomfort after the surgical removal of impacted mandibular third molars.

This study aimed to correlate and compare the impact of aescin and diclofenac on salivary PGE2 levels and serum C-reactive protein levels after surgical extraction of the mandibular third molar. The study will also evaluate and compare the effectiveness of individual drug therapy in managing postoperative pain, swelling and mouth opening.

**Methods:**

The planned study is a single-center, double-blind, randomized, parallel, prospective clinical trial. Each patient will be prescribed either diclofenac sodium 150 mg/day or aescin (escin) 120 mg/day to be taken orally in divided doses for five days after surgically removing the impacted mandibular third molar.

Pain will be assessed using a visual analog scale. Facial swelling and mouth opening will be recorded using a metric scale with standardized reference points. ELISA (enzyme-linked immunosorbent assay (ELISA) will be employed to measure salivary Prostaglandin E2 and serum C–reactive protein levels. All parameters will be recorded preoperatively (T0) on the second postoperative day (T1) and fifth postoperative day (T2).

**Conclusion:**

The proposed study is expected to show a clinically acceptable response to the administration of aescin for the management of postoperative discomfort compared to diclofenac sodium after third molar surgery.

The proposed study is expected to positively manipulate the levels of salivary Prostaglandin E2 and serum C–reactive protein, which are reliable inflammatory markers.

The outcome of this study may provide an efficacious and safe alternative to conventional nonsteroidal anti-inflammatory drugs for managing postoperative discomfort following third molar surgery.

## Introduction

### Background and rationale

The backbone of most oral surgical practices worldwide is the extraction of impacted third molars. It is the most common oral surgical procedure
^
1
^ performed in dental offices. However, the postoperative phase is often concomitant with severe pain, reduced mouth opening, and marked facial inflammation. Most patients are prescribed corticosteroids and nonsteroidal anti-inflammatory drugs (NSAIDs) to manage their postoperative discomfort. NSAIDS have been associated with gastrointestinal bleeding, disturbance in renal function, and a reduction in platelet count.
^
2
^ Certain newer NSAIDs like lornoxicam have been evaluated for their efficacy in managing pain after third molar surgery due to lesser incidences of gastrointestinal lesions as compared to other NSAIDs.
^
3
^ However, this untoward still poses a challenge to clinicians.

Because of these limitations, many phytotherapeutic alternatives have been suggested. Aescin (Escin) has generated interest among researchers over the years. It is a practical part of Aesculus hippocastanum and was first isolated in 1953. It combines triterpene saponins and has demonstrated anti-inflammatory, antiedematous, and venotonic properties in various preparations.
^
4
^ Thus, the present study demonstrates the utility of aescin in managing postoperative discomfort after the surgical removal of impacted mandibular third molars.

Another concern over the years has been the selection of NSAIDs, which predominantly depends on subjective factors, including the surgeon’s preference and personal experience. The need for an hour is to use a measurable marker of inflammation that can be quantitatively controlled by drug administration. Prostaglandin E2 (PGE2) is a reliable marker of inflammation, which has been isolated from various body fluids, including saliva.
^
5
^ Owing to inflammation, C-reactive protein (CRP) emerges in the blood. Various studies have used CRP concentrations to monitor the healing process after drug therapy because of its sensitivity.
^
6
^ This study aimed to correlate salivary PGE2 levels and serum C-reactive protein levels with subjective and objective symptoms after surgical extraction of the mandibular third molar and their relationship with therapeutic use of aescin and diclofenac. The objectives of the study is to compare the efficacy of aescin and diclofenac for managing pain, swelling, mouth opening and the need for rescue analgesics. The study will also evaluate the patient satisfaction regarding each drug therapy.

### Background and rationale: choice of comparators

Diclofenac was chosen for comparison because it has dose equivalence to aescin and is widely used to manage postoperative sequelae associated with third molar surgery.

## Protocol

### Aim of the study

To compare the efficacy of aescin (escin) and diclofenac in managing postoperative sequelae following surgical removal of impacted mandibular third molars and their effects on salivary Prostaglandin E2 and serum C-reactive protein levels.

## Objectives

The objectives of the present study are as follows:
1.To compare the efficacy of aescin and diclofenac sodium in managing postoperative sequelae following surgical removal of impacted mandibular third molars.2.To compare the efficacy of aescin and diclofenac sodium in manipulating salivary Prostaglandin E2 (PGE2) and serum C-reactive protein (CRP) levels in patients undergoing surgical removal of the impacted mandibular third molar.3.To assess patient satisfaction regarding therapy.4.To evaluate the need for rescue analgesics in the postoperative period.

### Trial design

A single-center, double-blind, randomized, parallel, prospective clinical trial will be conducted at the Sharad Pawar Dental College, Datta Meghe Institute of Higher Education and Research (DMIHER), Sawangi, Wardha.

Two groups will be created:

Group A – Diclofenac sodium

Group B – Aescin (escin)

The randomization process will be performed using a computer-generated subject allocation list.

Trial participants and outcome assessors will be blinded. The study will be a double-blinded clinical trial where the participant and the principal investigator will not be aware of the drug being used in the postoperative period. The double-blinded study minimizes the risk of various types of biases, such as observer bias or confirmation bias, which may influence the results of the investigation.

### Study setting

A total of 50 patients presenting to the outpatient department of oral and maxillofacial surgery, Sharad Pawar Dental College and Hospital, Sawangi, Wardha, India, with impacted mandibular third molars with a definitive indication for extraction will be enrolled in the study.

### Eligibility criteria

*Inclusion criteria*
1.Patients giving informed written consent.2.Age group 18-40 yrs. The age range is selected to have homogeneity, reduced comorbidities, relevance to the target population and better baseline functionality.3.ASA I and healthy ASA II physical status.4.Patients presenting with impacted mandibular third molars that are indicated for removal.5.Slightly or moderately difficult impacted mandibular third molars, according to the Pederson difficulty index with the difficulty score in the range of 3 to 7.

*Exclusion criteria*
1.Presence of oral mucosal comorbid conditions that may affect salivary inflammatory markers.2.Patients not reporting for follow-up as per study protocol.3.Presence of systemic infections that may alter the levels of serum C-reactive protein.4.Presence of acute infection that necessitates the use of antibiotic therapy.5.Known allergies to drugs under study and local anesthetic agents.6.Patients with a history of xerostomia or hypersalivation.

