### Surgical procedure

All patients will be administered 1 g of oral amoxicillin 1 h before the procedure. The standard surgical protocol for the removal of impacted mandibular third molars under local anesthesia will be followed.

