### Interventions: modifications

Drug therapy will be discontinued in cases of adverse reactions reported by the patient.

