### Interventions: concomitant care

Patients will be required to adhere to the standard postoperative instructions following extraction.

Tramadol 50 mg will be prescribed as a rescue analgesic for the postoperative period.

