### Blinding (masking): emergency unblinding

Unblinding will be performed if a patient reports adverse side effects to the emergency unit during the follow-up period.

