### Harms

Telephonic conversations will be conducted prior to follow-up visits to inquire about any untoward events. In case of any adverse events, patients will be managed at the institutional hospital, and the necessary care will be rendered free of cost.

All adverse events will be reported to the Institutional Ethical Committee.

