### Ancillary and post-trial care

The trial will be conducted in accordance with good clinical practice and a strong adverse event-monitoring protocol. The safety of the procedures and drugs used in this study has been established. However, in case of any harm, compensation will be carried out according to institutional policy.

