## Data Availability

No data is associated with this article. **Zenodo:** Extended data sheet for “Comparison of the efficacy of aescin and diclofenac sodium in the management of postoperative sequelae and their effect on salivary Prostaglandin E2 and serum C–reactive protein levels after surgical removal of impacted mandibular third molars: a randomized, double-blind, controlled clinical trial.”. Zenodo.
https://doi.org/10.5281/zenodo.10605612.
^
15
^ This project contains the following extended data:
•Model Consent form•Biological specimen•Patient Case Record form Model Consent form Biological specimen Patient Case Record form Zenodo: SPIRIT checklist for “Comparison of the efficacy of aescin and diclofenac sodium in the management of postoperative sequelae and their effect on salivary Prostaglandin E2 and serum C–reactive protein levels after surgical removal of impacted mandibular third molars: a randomized, double-blind, controlled clinical trial.”
https://doi.org/10.5281/zenodo.10605565.
^
16
^ Data are available under the terms of the
Creative Commons Attribution 4.0 International license (CC-BY 4.0).

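### The allergy exclusion does not name amoxicillin, which every patient is scheduled to receive before surgery

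*Protocol article*

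**What the plan says.** Item 5 of the exclusion criteria in the protocol article is the only criterion about drug allergy: "Known allergies to drugs under study and local anesthetic agents". The phrase for the study drugs is not defined. The Trial design section names two arms, diclofenac sodium and aescin, and Interventions: description gives their doses. Amoxicillin is not an arm. It appears under Surgical procedure: "All patients will be administered 1 g of oral amoxicillin 1 h before the procedure". No exception, allergy check or alternative antibiotic follows.

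The other safety provisions are these:

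- Interventions: modifications: "Drug therapy will be discontinued in cases of adverse reactions reported by the patient".
- Blinding (masking): emergency unblinding: "Unblinding will be performed if a patient reports adverse side effects to the emergency unit during the follow-up period".
- Harms: "In case of any adverse events, patients will be managed at the institutional hospital".
- Ancillary and post-trial care promises good clinical practice and adverse-event monitoring, and states: "The safety of the procedures and drugs used in this study has been established".

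A rescue drug is also planned: "Tramadol 50 mg will be prescribed as a rescue analgesic for the postoperative period".

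**The concern.** Two printed rules do not fit together safely. One decides who is kept out because of allergy; the other gives a penicillin to everyone who is let in. If the first does not cover the drug in the second, a candidate with a known penicillin allergy who meets the other criteria is eligible on paper and scheduled for the dose.

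This is a participant-safety matter only. Both arms receive the same antibiotic, so the treatment comparison, the C-reactive protein outcome and the sample size do not depend on it.

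**Working it through.** **Which drugs does item 5 cover?** There are two readings.

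- *Narrow:* the randomised drugs, diclofenac and aescin, plus local anaesthetics. This matches the arms in Trial design and explains why local anaesthetics needed their own mention.
- *Broad:* every drug given in the trial. The phrase is undefined, and Ancillary and post-trial care speaks generally of the drugs used, so this reading is possible. It would make the separate mention of local anaesthetics redundant.

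The narrow reading is the more natural one. On that reading, the authors extended the allergy rule to one non-randomised procedural drug and left out the other one given to every patient.

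**Does anything else act before the dose?**

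- Exclusion item 4 concerns acute infection that needs antibiotics, not allergy to them.
- The ASA inclusion criterion says nothing about allergy.
- Stopping therapy, unblinding and hospital care all follow a reaction or adverse event. Stopping therapy cannot undo a single dose already taken.
- Data Availability lists a "Patient Case Record form" as extended data. It is not shown. It may record allergy history, but recording a history is not an exclusion rule.

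No printed provision closes the gap beforehand.

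**Size.** The sample size is 2 × 25 = 50 patients (Study setting; Sample size), and amoxicillin is scheduled for all 50. The prevalence p of known penicillin allergy is not in the document, so it is an assumption, shown over 0.1% to 5%.

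- Chance that the printed criteria alone admit at least one such patient: 1 − (1 − p)^50
- Expected number admitted: 50p
- Candidates needed to enrol 50 if such patients are excluded: 50 / (1 − p)

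| Assumed p | Chance of at least one | Expected number | Candidates needed |
|---|---|---|---|
| 0.1% | 4.9% | 0.05 | 50.05 |
| 1% | 39.5% | 0.5 | 50.51 |
| 5% | 92.3% | 2.5 | 52.63 |

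The chance reaches one half at p = 1 − 0.5^(1/50) = 0.0138, or about 1.4%.

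**The case against.** The strongest reply is that the two rules do not contradict each other. An allergy exclusion can stand beside an antibiotic order, and nothing tells a clinician to override a known allergy. The surgical section is two sentences long and refers the rest to a standard surgical protocol, so arrangements for allergic patients may sit in the full protocol or the case record form, neither of which is shown. The trial runs in a hospital oral surgery department with ethics approval, where history-taking before giving a penicillin is routine. The study-drug phrase is undefined and could be meant broadly. The assumed prevalences span a 50-fold range and so cannot establish how serious the gap is. The discontinuation and unblinding rules do not really bear on a single preoperative dose.

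Much of this stands. Routine care would probably catch a known allergy, the probabilities rest on assumption, and inference is untouched. It does not remove the gap. The article prints both a specific allergy exclusion and a specific order for all patients, so their fit can be judged without the full protocol. Routine history-taking would apply equally to local anaesthetics, yet the authors wrote those in. If the broad reading was intended, the wording is unclear on a safety point and the same edit settles it.

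**Conclusion.** The concern holds, within the limits of the eligibility and dosing rules as printed. Followed literally, they would admit and dose a patient with a known penicillin allergy. The exposure taken from the document is 50 of 50 patients. The probabilities of 4.9% to 92.3% depend wholly on the assumed prevalence and describe eligibility before any history is taken; they are not a forecast of harm. The conclusion rests on the narrow reading of item 5, which is the more natural but not the only one. It should be corrected because it concerns safety and is cheap to put right; it does not threaten the validity of the results.

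Tramadol is a lesser instance of the same gap: item 5 does not name it either, but it is taken only as needed.

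**What to change.** Reword exclusion item 5 along these lines: *known allergy to diclofenac, aescin, local anaesthetic agents, or amoxicillin or any other penicillin*. Naming the drugs also removes the doubt about the undefined phrase. Adding tramadol is a sensible secondary change.

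Alternatively, keep penicillin-allergic patients eligible and name the substitute antibiotic under Surgical procedure.

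The first option costs a one-line amendment and one screening question. Over the assumed range it needs about 50.1 to 52.6 candidates to enrol 50, so at most about 3 extra. The second loses no candidates but means that a few patients receive a different antibiotic. Either change would go through the approval route in Protocol amendments. Study status places the trial at the pilot stage, so later participants could still benefit.

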## Methods

### Interventions: description

A clinical trial will be conducted with approval from the institutional ethics committee. The Consolidated Standards of Reporting Trials (CONSORT) statement guidelines will be used for this study.

Patients will be prescribed either diclofenac sodium 150 mg/day or aescin (escin) 120 mg/day
^
7
^ to be taken orally in divided doses for five days. Each patient will be subjected to one of the drugs after the procedure.

Saliva collection will be done using a sterile polystyrene tube. A kit specific to PGE2 will be used to measure PGE2 levels in each specimen.
^
5
^

Venous blood will be subjected to a C-reactive protein (CRP) test to measure C-reactive protein
^
8
^ levels in blood serum.

Saliva and serum samples will be processed in Central Research Laboratory.

### Surgical procedure

All patients will be administered 1 g of oral amoxicillin 1 h before the procedure. The standard surgical protocol for the removal of impacted mandibular third molars under local anesthesia will be followed.

### Interventions: modifications

Drug therapy will be discontinued in cases of adverse reactions reported by the patient.

### Interventions: adherence

Patients will be recalled on the second and fifth postoperative days. The number of tablets remaining will be calculated to assess compliance with the trial protocol.

### Interventions: concomitant care

Patients will be required to adhere to the standard postoperative instructions following extraction.

Tramadol 50 mg will be prescribed as a rescue analgesic for the postoperative period.

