## Outcomes

Postoperative sequelae after surgical removal of the impacted mandibular third molar will be estimated by assessing pain, facial swelling, and mouth opening.

Pain: The visual analog scale (VAS)
^
9
^ will be used to assess pain on a scale ranging from 0 to 10. The worst imaginable pain will be graded as 10, and the absence of pain will be graded as 0.

Facial swelling will be measured using a metric tape and standard reference points.
^
7
^ The following reference points will be used for the measurement:
•Soft tissue pogonion - Tragus•The angle of the mandible - Corner of the eye•Corner of mouth - Tragus

Mouth opening: The maximum interincisal distance will be recorded using a metric scale with standardized ruler and a digital Vernier caliper.
^
10
^

Salivary Prostaglandin E2 and serum C-reactive protein levels will be measured by ELISA (enzyme-linked immunosorbent assay (ELISA) preoperatively (T0) on the second postoperative day (T1) and fifth postoperative day (T2).

Patient satisfaction regarding therapy: Study subjects will classify their experience from 1 to 5, where 1 = poor, 2 = fair, 3 = good, 4 = very good, and 5 = excellent.

The need for rescue analgesics will be evaluated by counting the number of tramadol capsules or tablets required by the patient until the fifth postoperative day (T2).

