### Participant timeline

Pain, facial swelling, mouth opening, serum C-reactive protein, and salivary prostaglandin E2 levels will be recorded preoperatively (T0) on the second postoperative day (T1) and fifth postoperative day (T2).

Patient satisfaction regarding therapy and the need for rescue analgesics will be recorded on the fifth postoperative day.

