### Statistical analysis plan

**
*Statistics: outcomes*
**

**
*Statistics: additional analyses*
**

**
*Statistics: analysis population and missing data*
**

*Primary variable*

Inferential statistics will be used to compare the two groups for measurement scores, resulting in their mean change in a primary variable (visual analog scale, facial swelling, mouth opening, salivary prostaglandin E2, serum C-reactive protein) between baseline and end visits.

Baseline variables will be tested for significance in the mean using ANOVA or Kruskal-Wallis test for more than two assessment periods. A post-hoc (Tukey’s or Duncan’s) test will be used to find a significant difference between the two groups for pair-wise comparison.

*Outcome variables*

Outcome variables will be tested for intra-difference in measurement at pre- and post-visits using a paired t-test to determine the mean’s significance. The unpaired t-test for comparison of two groups and ANOVA for comparison of three groups will be used for intergroup differences.

Statistical analysis will be carried out using R-software free version.

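### Pain comparison only, a cheap improvement: VAS change is compared without reference to rescue tramadol, which is recorded as one cumulative total on day 5

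*Protocol article*

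**What the plan says.** Under Interventions: concomitant care, the protocol article provides that "Tramadol 50 mg will be prescribed as a rescue analgesic for the postoperative period". It gives no rule on when tramadol may be taken relative to a pain score.

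Under Participant timeline, VAS pain is among the measures taken before surgery (T0), on day 2 (T1) and on day 5 (T2). Tramadol use has one recording time: "Patient satisfaction regarding therapy and the need for rescue analgesics will be recorded on the fifth postoperative day". The Outcomes section defines it as "counting the number of tramadol capsules or tablets required by the patient until the fifth postoperative day (T2"), which is one running total.

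The Statistical analysis plan section compares the groups on "mean change in a primary variable (visual analog scale, facial swelling, mouth opening, salivary prostaglandin E2, serum C-reactive protein) between baseline and end visits". The test is given as "The unpaired t-test for comparison of two groups and ANOVA for comparison of three groups will be used for intergroup differences". Neither sentence mentions rescue.

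Rescue need is not forgotten. The end of the Background names it with pain, swelling and mouth opening in the efficacy comparison, and it is objective 4 under Objectives.

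**The concern.** Rescue use follows pain. A patient whose allocated drug works poorly takes tramadol, and tramadol lowers the VAS that is then scored. If one arm controls pain less well and so takes more tramadol, its VAS is pulled towards that of the other arm. A comparison of VAS alone then shows the allocated drug plus whatever rescue was needed.

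The article calls the trial non-inferiority (Sample size, Discussion) and expects a clinically acceptable response to aescin for postoperative discomfort (Abstract, Discussion). A pull towards similarity favours that expectation. At stake is whether similar VAS scores, reached with unequal tramadol use, would be read as similar pain control by the two drugs.

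The recording schedule matters more than the choice of test, because a later analysis plan can change the test. It cannot recover tramadol taken before the day-2 score from a day-5 total.

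**Working it through.** **Is the sample size involved?** The plan's only calculation uses serum CRP: 2 × (1.96 + 0.84)² × 3.977² / 3.261² = 23.3, which the plan gives as 23 per arm. No VAS or tramadol figure enters it, so nothing below changes it.

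**Do the windows match?**

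| VAS score | Tramadol information stated | What is missing |
|---|---|---|
| Day 2 (T1) | None at T1; only the total to day 5 | Use before T1 cannot be separated from use after it |
| Day 5 (T2) | Total to day 5 | Whether a dose was acting when VAS was scored |

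The comparison that the plan names runs from baseline to the end visit, the same window as the count. The day-2 gap therefore affects the T1 pain data, not that comparison. The day-5 gap does affect it.

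**How large could the shrinkage be?** The article gives no VAS figure for this trial. Its only VAS figures are in the Discussion: means of 2.58 on diclofenac and 3.46 on mefenamic acid in a background third-molar study, with no SD and no rescue rule.

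Inputs:
- Means without rescue: 2.58 and 3.46, borrowed from that study as if free of rescue (assumption).
- SD 2, normal, limited to the 0-10 scale (assumption).
- Patients at or above a VAS threshold t take tramadol, which lowers their score by r points; t = 4 to 7 and r = 1 to 3 (assumptions).
- Uptake u: all such patients (1) or half of them (0.5) (assumption).

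Formulas:
- Gap(t) = P(VAS ≥ t | mean 3.46) − P(VAS ≥ t | mean 2.58)
- Observed difference = D − u × r × Gap(t)
- Loss = u × r × Gap(t) / D

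Limiting the scale to 0-10 moves the means to 2.673 and 3.494, so D = 0.821.

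For t = 4, the standardised distances are (4 − 3.46)/2 = 0.27 and (4 − 2.58)/2 = 0.71. The shares rescued are 39.4% and 23.9%, a gap of 15.5 points. With r = 1, the observed difference is 0.821 − 0.155 = 0.666, and the loss is 0.155/0.821 = 19%.

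At full uptake:

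| Threshold | Rescued, worse vs better arm | Gap (points) | Observed difference, r = 1 / 2 / 3 | Loss, r = 1 / 2 / 3 |
|---|---|---|---|---|
| 4 | 39.4% vs 23.9% | 15.5 | 0.67 / 0.51 / 0.36 | 19 / 38 / 57% |
| 5 | 22.1% vs 11.3% | 10.7 | 0.71 / 0.61 / 0.50 | 13 / 26 / 39% |
| 6 | 10.2% vs 4.4% | 5.8 | 0.76 / 0.70 / 0.65 | 7 / 14 / 21% |
| 7 | 3.8% vs 1.4% | 2.5 | 0.80 / 0.77 / 0.75 | 3 / 6 / 9% |

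Half uptake halves every loss. If tramadol is acting at scoring in only half of its users, each loss halves again.

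**Sensitivity to the means.** With higher pain, assumed means 5 and 4 and SD 2, D is 0.98. The losses at full uptake are then 19 / 39 / 58% at thresholds 4 and 5, 15 / 30 / 46% at 6, and 9 / 19 / 28% at 7. Threshold 4 barely moves; the higher thresholds depend strongly on the assumed level of pain.

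**The case against.** The strongest reply is that the trial already measures rescue need as an efficacy outcome and would report it beside VAS. Comparing VAS as observed, with rescue allowed and counted separately, is a legitimate choice. This stands, and it is why neither rescue care nor the planned test needs to change. It does not supply the missing timing, and no sentence says that the two results will be read together.

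A second reply is that the handling of rescue in the analysis belongs in an analysis plan that is not shown. This also stands for the method. It does not cover the recording time, which the article itself fixes at day 5.

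A third reply is that the day-2 visit already has a tablet count: "The number of tablets remaining will be calculated to assess compliance with the trial protocol". Its stated purpose is compliance and tramadol is not named, so it cannot be taken as a rescue count. The case record form, listed under Data Availability but not shown, may date each dose. If it does, the timing gap closes.

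A reader might infer two stronger points. One is that the day-2 mismatch undermines the planned VAS comparison; it does not, because that comparison ends at day 5, where the count also ends. The other is that unequal rescue could produce a false finding of non-inferiority. The documents do not support this: the only margin is for CRP, none is stated for pain, and no decision is shown to turn on the VAS difference.

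**Conclusion.** The point holds as a modest improvement to the pain comparison. As written, VAS change is tested without reference to tramadol, and the single day-5 total neither splits at day 2 nor shows whether a dose was acting at day 5. Any bias runs towards similarity if the less effective arm takes more tramadol, a condition that the documents neither establish nor rule out.

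Its size cannot be derived from the documents. On the background means it runs from about 3% to 57% of the true VAS difference at full uptake, and half that at half uptake. The range rests on an assumed SD, threshold and tramadol effect, and on means that may themselves already include rescue. The low thresholds drive the upper end; if patients take tramadol only for severe pain, the effect is small.

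**What to change.** Leave rescue care and the planned VAS test as they are.

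1. Count tramadol at T1 as well as T2, and note the time of the last dose before each VAS. No extra visit is needed: "Patients will be recalled on the second and fifth postoperative days. The number of tablets remaining will be calculated". If the case record form already dates each dose, skip this step.
2. Report the VAS result together with the between-group difference in tramadol use and its 95% interval.
3. Add one sensitivity analysis that ranks patients jointly on VAS and tramadol use, so that a low score reached with more tramadol does not count as equal to one reached with less.

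The cost is an extra form item, a short extra analysis, and a pain claim that is slightly harder to reach. Study status describes the work as at the pilot stage, so the form change may still be possible. Day-2 use that is not captured at the time cannot be reconstructed from the total.
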